### Harms

2.10

To collect, assess, report, and manage the potential adverse effects of the interventions, at the beginning and end of each treatment session, patients from both groups will have a logbook available. According to the informed consent for patients, those who show an increase in symptoms within 48 hours after the session will require an immediate evaluation by an orthopedic surgeon.

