Surgical options include partial repair and/or debridement, repair (open or arthroscopic), reconstruction (muscle transfer or processed tissue), and arthroplasty (hemi or reverse shoulder).^[22,23]^ The widespread use of arthroscopy has been related to a significant increase in RC repair procedures in recent decades,^[24]^ and currently arthroscopic repair has replaced open surgery and is now used to treat greater than 95% of all RC tears.^[25]^ Although the arthroscopic RC repair decreased pain, earlier functional recovery, and lower re-tears rates compared to open or mini-open procedures,^[26,27]^ a number of complications still occur in association with all types of RC repair.^[28]^ The overall rate for self-reported surgical complications after arthroscopic shoulder procedures is 7.9%,^[29]^ being the shoulder stiffness and residual pain the most reported.^[29,30]^

Following arthroscopic RC repair, a period of movement restriction is advised^[31]^; however, the optimal time of immobilization is unknown. It is common a practice to ask patients to use a sling for 6 weeks and avoid activities with the affected shoulder.^[32,33]^ This period is important to protect the tendon, allow healing, and prevent re-tear events.^[34]^ However, delayed motion may increase the risk of postoperative shoulder stiffness and muscle atrophy and delay functional recovery.^[32]^ Based on the available evidence, it is difficult to make a clinical decision about the best rehabilitation regime and establish the most favorable time to start the postoperative rehabilitation program.^[35]^ In recent years, there is still controversy regarding the influence of early versus delayed motion on stiffness and healing rate after RC repair.^[36]^ It is known that early motion rehabilitation increases range of motion (ROM) after RC repair,^[37–41]^ but the risk of re-tear is significantly higher compared to immobilization.^[38,39,42]^ Immobilization can result in stiffness of the shoulder, which can cause pain, functional limitations, and frustration for patients.^[43]^

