### Interventions

2.3

The control group will receive a standard exercise program based on the consensus statement on shoulder rehabilitation developed by the American Society of Shoulder and Elbow Therapists (ASSET).^[45]^ This exercise program proposes a 2-week period of strict immobilization and a staged introduction of protected, passive ROM during weeks 2 to 6 postoperative, followed by restoration of active ROM beginning at 6 weeks, with a gradual strengthening progression beginning at 12 weeks postoperative.^[45]^ In stage 1 (0–6 weeks), the first 2 weeks will be of strict immobilization with a sling, then a passive protected ROM with limits of <90° of forward elevation and <20° of external rotation will be performed during weeks 2 to 6. The specific components of this stage are the following:

(1)patient education: important points of emphasis in education include understanding of the pathology and procedure, time frame for recovery, the associated precautions during each stage of the treatment, and the importance of a home exercise program;(2)cryotherapy: the subjects receiving cryotherapy in the first 10 days postoperatively^[53]^; and(3)a home exercise program based on passive and self-assisted exercises.

In this first stage of rehabilitation, the exercises chosen for passive ROM should have levels of EMG muscle activity ≤15% and should be performed only in a gentle and comfortable manner. Four exercises will be performed: self-assisted supine forward elevation 60° to 90°^[54–56]^; self-assisted external rotation with stick at 20° of glenohumeral abduction^[54,55]^; active motions of the elbow, wrist, and hand (no external weight); and pendulum exercise.^[54,55,57]^ This will be performed once a day for 2 weeks.

In stage 2 (6–12 weeks), a supervised exercise program based on active or active-assistive ROM with limits of <120° of forward elevation and <30° of external rotation will be performed. The exercises within this category use gravity-minimized positions, such as supine or side lying and/or short lever arms to promote RC and deltoid balance.^[58,59]^ Six exercises will be performed: towel slide or horizontal dusting^[47,56]^; active-assistive ROM supine washcloth press-up^[56]^; active ROM supine press-up^[56]^; side-lying supported active elevation^[47]^; active ROM reclined wedge press-up^[56]^; and supine elastic band forward elevation.^[47]^

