The intervention group will receive a supervised early exercise program in combination with the standard exercise treatment. This exercise program will be based on EMG evidence (Fig. 2). Stage 1 (0–4 weeks), the first 2 weeks will be of strict immobilization with a sling, and 5 exercises will be performed generating remote or indirect activation of the RC with levels of EMG muscle activity ≤20% of MVIC: “belly press exercise with biofeedback” with an activation less than 20% MVIC for supraspinatus,^[60,61]^ “isometric hand grip task” with 90° elbow flexion with an activation less than 20% MVIC for supraspinatus,^[62,63]^ “isometric finger extension exercise” for infraspinatus muscle activation with 90° elbow flexion with significant activation of voluntary remote contraction,^[64]^ “isometric wrist flexion” to supraspinatus muscle activation in sitting position with an activation of less than 20% MVIC^[65]^, and “scapular depression” in sitting position with a 13% MVIC activation for supraspinatus.^[66]^

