**Figure 2 F2:**
[figure not shown]
Detailed description of the supervised early exercise program.

Stage 2 (4–6 weeks), 4 exercises will be performed: “isometric elbow flexion” for supraspinatus and upper subscapularis in sitting position,^[67]^ “scapular conscious control” for generating scapular retraction and scapular muscles activation,^[68]^ “isometric adduction” for infraspinatus and subscapularis activation,^[69]^ and “forward bow exercise” for supraspinatus and infraspinatus activation in sitting position.^[67]^ Additionally, 2 passive ROM exercises will be performed: passive external rotation and anterior flexion in supine position. These exercises will be assisted by at therapist.^[70]^

For control and intervention group the exercises should not produce pain; only mild to moderate pain levels (<4/10 on the visual analog scale [VAS]) are accepted after the session. Dose will be related to the goal of each exercise and will be adjusted in relation to the individual patient. From 8 to 10 repetitions of each exercise will be performed, with 5 to 10 seconds of task maintenance and 30 seconds to 1 minute of rest between each repetition. There will be 3 weekly sessions for 6 weeks.

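### Harms are recorded at treatment sessions, and in weeks 0–6 the two arms probably do not have the same sessions, so recorded adverse-event rates may not be comparable

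*Protocol article*

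**What the plan says.** Section 2.10 (Harms) gives the recording rule: "at the beginning and end of each treatment session, patients from both groups will have a logbook available". It adds an escalation rule with the same anchor: "those who show an increase in symptoms within 48 hours after the session will require an immediate evaluation by an orthopedic surgeon". The article describes no other route for collecting harms.

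Section 2.3 (Interventions) sets out who has sessions and when.

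- **Control, weeks 0–6.** The listed components are education, cryotherapy and "a home exercise program based on passive and self-assisted exercises". After listing the four exercises the text says "This will be performed once a day for 2 weeks".
- **Control, weeks 6–12.** Supervision is stated for this arm for the first time: "In stage 2 (6–12 weeks), a supervised exercise program based on active or active-assistive ROM".
- **Intervention.** "The intervention group will receive a supervised early exercise program in combination with the standard exercise treatment". Its two stages cover weeks 0–4 and 4–6, and some of the exercises are therapist-assisted.
- **Frequency.** The last paragraph of section 2.3 opens by addressing both groups and closes with "There will be 3 weekly sessions for 6 weeks". It does not say which calendar weeks are meant, or whether they are the same weeks in both arms.

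Section 2.4 schedules assessments before surgery, at 6 weeks and at 12 weeks in both arms. The measures listed there are efficacy outcomes and potential confounders; harms are not among them. On early motion after repair, the Introduction says "but the risk of re-tear is significantly higher compared to immobilization".

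**The concern.** When harms are noted at treatment sessions, and treatment sessions are what differs between the arms, the chance of recording an event depends on allocation as well as on whether the event happened. Giving both groups a logbook equalises access to it, but not the number of occasions on which it is due to be completed.

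The timing makes this matter. The added supervised program occupies weeks 0–6. The Introduction describes the early restricted period as one that protects the tendon and helps prevent re-tear, and it reports more re-tears with early motion. A reader of the results will want to know whether the added program is as safe as standard care. If events are noted more often in the intervention arm only because there are more occasions to note them, the program can look harmful when it is not. If the control rate is under-recorded, there is also no sound comparator to support a claim of safety. Patients and therapists are unblinded, so prompting at sessions could add to the difference. Control-arm events that were never noted cannot be recovered later.

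**Working it through.** The article gives no figure on harms to reproduce, and the sample-size calculation does not enter. The check is a count of recording occasions per arm in weeks 0–6 under each reading of what a session is.

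**Inputs**

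- Session frequency: 3 per week for 6 weeks (section 2.3, last paragraph).
- Log points per session: 2, start and end (section 2.10).
- Control home exercise: once a day for 2 weeks (section 2.3), i.e. 7 × 2 = 14 home sessions. If the exercises instead run daily through weeks 2–6, the count is 7 × 4 = 28. This second figure is an assumption.
- The intervention arm also receives standard treatment, so home sessions are added to its count.

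**Supervised sessions:** 3 × 6 = 18, or 18 × 2 = 36 log points.

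| Reading of the session rule, weeks 0–6 | Intervention | Control | Ratio |
|---|---|---|---|
| A. Only supervised sessions count | 18 | 0 | not defined |
| B1. Home sessions count, 14 of them | 18 + 14 = 32 | 14 | 32/14 = 2.3 |
| B2. Home sessions count, 28 (assumed) | 18 + 28 = 46 | 28 | 46/28 = 1.6 |
| C. Both arms attend 3 times a week in weeks 0–6 | 18 | 18 | 1.0 |

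In log points, A is 36 against 0, B1 is 64 against 28, and B2 is 92 against 56. Under B1 and B2 every control entry is made without supervision, while the intervention arm has 18 supervised sessions as well.

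**Which reading fits the text?** Reading C needs control patients to attend three times a week during a stage whose listed exercise component is a home program and for which no supervised session is described. The frequency sentence can apply to both groups without giving reading C: the control arm's supervised stage, weeks 6–12, also lasts 12 − 6 = 6 weeks. On that view each arm has its 18 sessions, but in different calendar periods, and the early count remains as in A or B.

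**From occasions to bias.** If the true risk is equal, the apparent risk ratio is (capture probability, intervention) / (capture probability, control). Capture of 0.9 against 0.6 gives 0.9/0.6 = 1.5; 0.9 against 0.3 gives 3.0. These capture values are assumptions and the result merely restates them. They show the direction and mechanism, and are not an estimate for this trial.

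**The case against.** The strongest reply is that the text does not establish an 18-to-0 imbalance. The paragraph containing the session frequency begins with both groups. Section 2.10 itself speaks of sessions for patients in both groups. Section 2.2 sends every patient to the Physical Therapy Department two days after surgery. That the control arm has no department sessions in weeks 0–6 is inferred from silence. This stands as far as it goes: a reader might conclude that the control arm has no recording occasions at all in that period, and the document does not support so firm a statement. Nor does it say that a therapist must complete the logbook or that home sessions are excluded.

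Second, a reader might infer a spurious risk ratio of a definite size. The document gives neither event rates nor capture rates, and fewer scheduled entries need not mean that a serious or lasting event is missed.

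Third, some measurement is symmetric. The Introduction names stiffness and residual pain as the most reported complications of arthroscopic shoulder procedures. Passive range of motion and pain are measured in both arms at 6 and 12 weeks, by assessors whom the Discussion describes as blinded and outside the research team. This also stands, although these are outcome scores at two postoperative time points and not a record of events between them.

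Fourth, a reader might fault the article for not naming re-tear as an event to record. A condensed article commonly leaves event lists to the full protocol, so that is not held against it.

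What the reply does not remove is the rule itself. Recording is anchored to sessions, and only reading C, the one that fits the home program poorly, makes the occasions equal.

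**Conclusion.** The point holds in a limited form. The stated rule links harm ascertainment to sessions, and on the most natural reading of section 2.3 these differ by arm in weeks 0–6: 18 against 0 counting supervised sessions only, or about 1.6 to 2.3 to 1 counting home sessions. The upper end of that range uses the printed two weeks of daily exercise; the lower end assumes daily exercise through weeks 2–6. Recorded adverse-event rates may therefore not be comparable between arms, with fuller recording more likely in the intervention arm. The size of the bias cannot be derived from the document. The conclusion would fall if both arms were shown to have the same sessions in weeks 0–6, or if the full protocol collects harms by a route that does not depend on sessions.

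**What to change.** 1. Collect harms independently of treatment sessions: the same logbook, completed on the same fixed calendar days in both arms, from surgery to week 12.
2. Add one identical structured harms question at the existing 6- and 12-week visits, covering any re-tear, stiffness or reoperation diagnosed since the previous visit. Tabulate the answers by arm. Asking it after the outcome measurements keeps an answer that reveals allocation from influencing them.
3. Do not use the session-triggered orthopedic evaluations as the source for between-arm counts, because they would carry the same asymmetry forward. This concerns counting only; the clinical rule itself is not at issue.
4. Reconcile sections 2.3 and 2.10: say what counts as a session for the logbook, and which arm and which weeks the three weekly sessions cover.

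The cost is a few extra minutes of logging for patients, one question per visit, and revised logbook instructions. No additional visit, imaging or change in sample size follows.

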### Ethics

2.11

The study will be conducted under the Declaration of Helsinki principles,^[88]^ as well as following the norms of good clinical practice. The study protocol has been approved by the Ethical Committee of the Central Metropolitan Health Service of Chile. This research was registered in the Brazilian Registry of Clinical Trials with the number U1111-1224-4143.

## Discussion

3

The aim of this article is to describe the rationale and methods of a randomized controlled trial to test the effectiveness of 2 exercise programs in adult with arthroscopic RC repair. The control group will receive a standard exercise program based on a consensus statement on shoulder rehabilitation developed by the ASSET.^[45]^ The intervention group will receive a supervised early exercise program in combination with standard treatment. This supervised exercise program will be based on EMG evidence.

Despite the high incidence of surgery for RC repair, there is no consensus on the most effective approach for postoperative rehabilitation^[89,90]^ due to available evidence on timing and the load on the recovery process of tendon healing.^[34]^ Studies have shown that early motion increases ROM after RC repair^[37–41]^; however, the risk of re-tear is significantly higher compared with immobilization.^[38,39,42]^ Additionally, immobilization can result in shoulder stiffness, pain, functional limitations, and frustration for patients.^[43]^ Therefore, it is difficult to take a clinical decision about the best rehabilitation program. Nevertheless, the influence of these protocols on tendon healing and functional outcome is not well known.^[91–93]^

Usually, orthopedic surgeons prescribe a short period of immobilization and early passive mobilization to minimize stiffness; however, the type of immobilization, position, and shoulder motion remain unclear for tendon healing.^[42,94,95]^ Second, a home exercise program has not been developed, because factors such as age, tobacco use, comorbidities, and intrinsic tendon characteristics can be confounding factors for prescribe a home exercise program.^[40,42,95]^

Currently, strict immobilization time ranges from 0 to 6 weeks, where exercises are not prescribed to protect the surgery.^[90]^ Evidence needs from protocols describing important characteristics of a supervised early exercise program such as; an indirect and low load neuromuscular activation of the RC muscles, according to previous EMG studies, the load is less than 20% MVIC without overloading the repaired tendon.^[44,45,47,48]^ This protocol also describes other characteristic, a short duration isometric contraction muscular without compressive load in tendon, with a hypoalgesic action.^[96]^

Furthermore, this isometric exercise has other characteristics. First, this neuromuscular activity does not cause damage to the repaired tendon. Second, the short duration and low load do not have the possibility of generating muscle fatigue. And third, the exercises are supervised with a biofeedback based on motor skills training to reorganize cortical plasticity and achieve motor learning.^[97–99]^

To strengthen the reliability of the results, important methodological factors have been considered when planning this study. To avoid selection bias, a clinical and imaging diagnosis of RC will be considered, including echotomography and magnetic resonance imaging; and participants will randomly be assigned to the groups through a hidden allocation sequence. Furthermore, adjusting the sample size for possible losses or dropouts and increasing the number of patients recruited by 20% were considered; in the event of loss or withdrawals, statistical analysis will be carried out by protocol and intention to treat. To minimize measurement bias, all evaluations will be performed by 2 physiotherapists outside the research team, who will also remain blinded in relation to the treatment groups; the statistician will remain blinded to the group assignment of the participants. Finally, the outcome measures are suitable and frequently used in clinical practice, and they have good levels of validity and reliability.

Our study has some limitations. One important limitation is that the supervised early exercise program will be based on EMG evidence and has not yet been validated. Furthermore, the absence of follow-up once both treatments will be finalized, which does not allow establishment of the effectiveness of the therapeutic intervention in the long term. Finally, blinding of physiotherapists and patients was not achievable given the nature of the interventions studied.

To the best of our knowledge, this is the first clinical trial that studies a supervised early exercise program based on EMG evidence in combination with the standard exercise program based on the ASSET consensus statement, compared to a standard exercise program alone. The results of this study will add evidence to the limited and controversial body of knowledge related to the effectiveness of the different modalities of therapeutic exercises that are prescribed for patients with arthroscopic RC repair.
